### Data Monitoring and Ethics Committee (DMEC)

An independent DMEC has been established for the trial. For the duration of recruitment, interim analyses will be supplied by the trial statistician, in strict confidence, to the DMEC, together with any other analyses the DMEC may request. The data will be supplied to the Chair of the DMEC as often as he requests. Meetings will be arranged periodically, as considered appropriate by the Chair. In the light of interim data, and other evidence from relevant studies, the DMEC will inform the principal investigator ([name]), if in their view (i) there is proof beyond reasonable doubt that the data indicate that any part of the protocol under investigation is clearly indicated or contra-indicated, either for all participants or for a particular subgroup of trial participants, or (ii) it is evident that no clear outcome will be obtained.

The decision to inform the principal investigator in either of these circumstances will, in part, be based on statistical considerations. Appropriate criteria for proof beyond reasonable doubt cannot be specified precisely. A difference of at least three standard deviations in the interim analysis of the major endpoint may be needed to justify halting, or modifying, such a study prematurely. If this criterion were to be adopted, it would have the practical advantage that the exact number of interim analyses would be of little importance, and so no fixed schedule is proposed [13]. Unless modification or cessation of the protocol is recommended by the DMEC, the principal investigator, co-investigators, collaborators and administrative staff will remain ignorant of the results of the interim analyses. Collaborators and all others associated with the study may write to the Chair of the DMEC to draw attention to any concern they may have about the possibility of harm arising from the treatment under study, or any other matter that may be relevant. The principle investigator will follow the advice of the Chairman concerning decisions to continue or stop the trial.

The members of the DMEC for this study are:

[name], Dept of Medicine Intensive Care Unit, Peking Union Medical College Hospital (Chairman)

[name], Dept of Medicine, University of Peradenya, Sri Lanka

[name] Dept of Medicine, Dhaka Medical College, Bangladesh

[name] [name], Hong Kong Poison Control Center, Hong Kong, China

[name], Dept of Statistics, Peking Union Medical College Hospital (Statistician)

## Discussion

The GLAOP study is a multi-site, prospective cohort study that seeks to evaluate the impact of gastric lavage, particular OP and ingestion time etc. on a variety of important outcomes. Whereas previous studies of gastric lavage have measured the outcomes in drug overdosers[8], the GLAOP study is distinguished by its large sample size of OP patients and its comprehensive measurement of poison levels. Building on these strengths allows the GLAOP study to evaluate the impact, and associated mechanisms of gastric lavage action on longer-term patient outcomes, and to generate hypotheses for future research. Ultimately, the GLAOP study seeks to inform clinicians about the gastric lavage therapy in pesticide poisoning, so as to facilitate change in clinical practice and improve outcomes for pesticide poisoning patients. The GLAOP study has potential limitations. First, besides times of gastric lavage, there are many known factors influencing the result. These include ingestion time, particular OP, amount of ingestion, the underlying disease and so on. Furthermore some important factors may be unknown or unmeasured, resulting in residual confounding and bias. If these differences are associated with the outcomes of interest, the study results may be difficult to analyze. Fortunately, software for the randomization has been used in the triage of the trial. Second, because of the ethic concern, group without lavage at all can not be set up in China to investigate its role in OP patients directly. No matter what result was put out, single lavage better or multiple lavages better, it is difficult to put forward the trial further because of the different ethic concerns in the world. For example, if multiple lavage shows no better than single lavage, it is a long journey to set up a RCT to explore the difference between single lavage and no lavage in China. Third, although drawn from 3 different medical centers and a treatment protocol has been used, all these hospitals are in China; thus, the GLAOP study results may not generalize to OP patients in other settings.

These limitations suggest several directions for future studies. First, the design of future randomized trials of gastric lavage. Narrow the inclusion criteria of OP patients, then the respective factors can be studied better. Second, in order to put forward relative studies thereafter, communications with experts in the world are necessary. Winning the understanding of the trial and its importance, it will be better to accomplish the trials. Finally, additional observational studies especially taken outside of China should be conducted to assess the generalizability of findings from the GLAOP study.

In summary, the GLAOP study is a prospective cohort study that seeks to provide new knowledge about the association of gastric lavage, particular OP and other aspects of OP with the patient outcomes. Strengths of the study include comprehensive measurement of samples and outcomes, and a relatively large projected sample size. Results from the GLAOP study should help to explore to the toxic kinetics of OP and effects of gastric lavage on it, help to improve the care and outcomes of OP patients.

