### Allocation of patients

Patients will be randomised to one of two study arms. The random allocation sequence will be generated by computer and incorporated into a Microsoft Access programme written for patient recruitment, randomisation and event recording. Stratified block randomisation will be performed according to patient status on admission (Glasgow coma score 14–15/15, Glasgow coma score <14/15).

The allocation sequence will be generated independently by the study statistician and programmer, who will have no role in patient recruitment, treatment or assessment. Variable block sizes of 3, 6 and 9 will be used to allocate patients in equal numbers to each treatment group i.e. ratio 1:1.

Participants will be recruited and randomised by a study doctor at the bedside using a dedicated handheld computer at each study hospital. Randomisation will occur after the patient's baseline data have been entered and receipt of consent noted, and cannot be manipulated by study doctors. The recruiting doctor will be unable to predict allocation before randomisation.

All practical steps have been taken to avoid bias: (i) the randomisation program has been designed to be rapid and simple to operate, and yet remain independent of the investigators; (ii) the next treatment allocation cannot be predicted in advance; (iii) the primary outcome, vital status at discharge, is unambiguous, and the secondary outcomes are objective; (iv) all outcomes are recorded by the study team, not other hospital physicians;

(v) patient follow-up should be near 100% complete; and (vi) the analysis will be performed on an intention-to-treat basis.

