### Outcomes

The primary outcome is all-cause mortality during hospital admission.

Secondary outcomes include proportion of patients requiring intubation for respiratory failure; period of ventilation; proportion of patients developing the intermediate syndrome; and 50% recovery time for red cell acetylcholinesterase enzyme activity.

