### Sample size

In all three patient enrolled hospitals, at least 15% of poisoned patients die before discharge[6]. An absolute reduction of 6% will be clinically important. In order to be able to detect whether multiple gastric lavage reduces the death rate from 15% to 9%, with a significance level (alpha) of 5% and a power of 80%, a minimum of 454 patients must be recruited to each arm of the trial (i.e. 908 patients in total).

There should be no loss to follow up for the primary outcome. Patients will either be discharged alive from the wards or their bodies transferred to the morgue for judicial autopsy. Secondary clinical outcomes will be assessed in hospital before patient discharge; red cell AChE will be measured in a subset of patients by a laboratory blind to allocation.

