### Study hypotheses and planned analyses

The main hypothesis is that multiples gastric lavages will reduce the case fatality rate from 15% to 9%, hence the primary comparison will be of multiple lavages with a single lavage.

It is possible that multiple lavages will be more effective the earlier they are started. Therefore we will assess the trends in clinical effectiveness according to time post-ingestion to start of therapy. In order to determine whether treatment should be started irrespective of severity, we will also assess trends in case fatality rates across a gradient of severity.

Subgroup analyses are planned to look at the consistency of treatment effect across particular OPs that are common in China, eg. dichlorvos, phorate, dimethoate. Analyses will also be done to check whether ingestion of a meal within one hour of the ingestion affects outcome.

Admission blood and stomach content samples will be retrospectively analysed to determine the identity of the poison ingested. The primary analyses will then be repeated with correction for the identity of the poison. The time-dependent variations of OP level will be analysed in order to provide OP toxic kinetic data.

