### Statistical analysis

The main analysis will be carried out on an intention-to-treat basis, using the chi squared test for the primary outcome (or Fisher's exact test if appropriate) and for other dichotomous outcomes. Relative risk (plus risk reduction), absolute risk reduction and number needed to treat (plus 95% confidence intervals) will also be calculated. For outcomes where time-to-event is recorded, the log rank test will be used to compare treatment groups. In addition, a Kaplan-Meier curve will be produced to illustrate the comparison of mortality between groups.

An analysis of trends in treatment effect for factors 'reported time from ingestion to treatment' and 'patient status on admission' will also be performed using statistical modelling techniques.

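### The primary comparison of mortality is unadjusted, although time since ingestion and coma score are known before randomisation; the test stays valid, but some precision is given up

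*Protocol article*

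**What the plan says.** All references are to the protocol article.

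- **Outcomes:** "The primary outcome is all-cause mortality during hospital admission".
- **Statistical analysis:** the main analysis is by intention to treat, "using the chi squared test for the primary outcome (or Fisher's exact test if appropriate) and for other dichotomous outcomes". Relative risk (RR), absolute risk reduction (ARR) and number needed to treat (NNT) follow, with 95% confidence intervals. No covariate or stratum term is named. Time to treatment and admission status are modelled, but for trends in the treatment effect.
- **Study hypotheses and planned analyses:** one adjusted repeat is planned: "The primary analyses will then be repeated with correction for the identity of the poison". Identity is determined later, from admission samples.
- **Inclusion and exclusion criteria:** patients must present within 12 hours of ingestion.
- **Allocation of patients:** randomisation is stratified by Glasgow coma score (14–15 against below 14). "Randomisation will occur after the patient's baseline data have been entered". The baseline variables are not listed.
- **Discussion:** "besides times of gastric lavage, there are many known factors influencing the result". The examples are ingestion time, the particular organophosphate, amount ingested and underlying disease. The answer offered is the randomisation software.

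**The concern.** The Discussion treats differences in prognostic factors as something that could make the results hard to analyse. For measured factors there is a standard answer, which is to adjust the main comparison for values known before randomisation. The stated primary analysis does not do this.

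At least two such values must exist for every randomised patient. Eligibility cannot be judged without the time since ingestion, and the stratum cannot be assigned without the coma score. Both are plausible predictors of death. Leaving them out means a wider confidence interval and lower power than the same 908 patients could give. The sample size leaves no margin above 80% power, so even a small gain has some value.

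**Working it through.** **1. Inputs from the article.** Sample size section: "detect whether multiple gastric lavage reduces the death rate from 15% to 9"%, "with a significance level (alpha) of 5% and a power of 80"%, 454 per arm (908 in total), no loss to follow-up. Allocation is 1:1. Sidedness is not stated.

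**2. Reproducing the planned size (two-sided, unadjusted).**
- Pooled: n = [1.960·√(2·0.12·0.88) + 0.842·√(0.15·0.85 + 0.09·0.91)]² / 0.06² = 460 per arm.
- Unpooled: n = (1.960 + 0.842)²·(0.1275 + 0.0819) / 0.06² = 456.5, so 457.
- Arcsine: n = 2·(1.960 + 0.842)² / h², with h = 2·asin√0.15 − 2·asin√0.09, gives 453.7, so 454.
- Power at 454 per arm (pooled formula): 79.5%.

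The stated size is therefore that of a two-sided unadjusted test.

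**3. Power with adjustment, by formula.** If baseline covariates explain a share R² of the outcome variance, the effective size is about 454/(1 − R²) and the standard error shrinks by √(1 − R²). R² is an assumption, because the article gives no prognostic strength.

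| Assumed R² | SE ratio | Power |
|---|---|---|
| 0 | 1.000 | 79.5% |
| 0.05 | 0.975 | 81.5% |
| 0.10 | 0.949 | 83.6% |
| 0.20 | 0.894 | 87.6% |
| 0.30 | 0.837 | 91.5% |

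**4. Simulation with one baseline score.** 2,000 trials per scenario, 454 per arm, marginal risks 15% and 9%; chi-squared against logistic regression on arm and score.

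| R² (c-statistic) | Crude power | Adjusted power | Gain (points) |
|---|---|---|---|
| 0.03 (0.63) | 79.4% | 79.6% | 0.2 |
| 0.12 (0.75) | 79.9% | 84.1% | 4.2 |
| 0.22 (0.82) | 79.9% | 87.4% | 7.5 |

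Type I error was 4.3–5.5% crude and 4.6–5.4% adjusted.

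**5. How much comes from beyond the coma stratum.** A second simulation (2,500 trials per scenario) assumed 35% of patients with a coma score below 14 and a log odds ratio of 1.2 for that stratum. It also assumed effects of time since ingestion and of one further severity score.

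| Joint c-statistic | Crude | Stratum only | All factors | All minus stratum (points) |
|---|---|---|---|---|
| 0.70 | 80.5% | 81.6% | 83.0% | 1.4 |
| 0.74 | 80.2% | 81.4% | 83.4% | 2.0 |
| 0.78 | 80.2% | 81.2% | 85.5% | 4.3 |

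Type I error of the full model was 4.8–5.3%. The last column credits time and the extra score together. The article describes no such score, so time alone may give less.

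**6. Size of chance imbalance.** For a binary factor present in half the patients, the SD of the between-arm difference in prevalence is √(0.25·2/454) = 3.3 points. Assume 5% mortality without the factor and 25% with it. A 1.96-SD imbalance then shifts the risk difference by 1.96 × 0.033 × 0.20 = 1.3 points. The standard error of the risk difference is √(0.1275/454 + 0.0819/454) = 2.1 points and the target effect is 6 points.

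**The case against.** The strongest reply is that nothing here is wrong. A crude intention-to-treat comparison of a binary outcome in a 1:1 trial is valid, and it matches the test behind the sample size. Choosing an adjusted primary analysis is a preference between two valid methods, and a covariate list for a supporting model commonly belongs in a statistical analysis plan that is not shown. The validity argument stands in full. The second argument stands only in part: the article does not leave the primary method open but states a crude one, and the suggestion is a specific change to that method.

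Three stronger readings are tempting, and the document does not support them.

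- **Chance imbalance biases or invalidates the result.** A reader might infer this from the Discussion. Randomisation protects the crude test, its error rate stays near 5%, and step 6 shows that even an unlucky draw on a strong factor moves the estimate by less than one standard error. The Discussion's worry about unmeasured factors cannot be met by adjustment at all; randomisation is the right answer to it.
- **The plan adjusts for nothing.** Poison identity, one of the four named factors, is corrected for in a planned repeat. Being assayed later does not disqualify it, since the poison was swallowed before randomisation. Time and admission status are modelled too, and an interaction model would normally contain their main effects. However, the stated purpose is effect modification, and no adjusted overall effect is promised.
- **All the named factors are available at no cost.** The article does not show that amount ingested or underlying disease is recorded before randomisation. Time is as reported, and unconscious patients enter through relatives, so missing or unreliable values are plausible.

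**Conclusion.** The point holds as one of efficiency, not validity. The primary comparison ignores two baseline values that must be known before randomisation, one of which the article itself names as influencing the result. The only stated adjusted repeat of the primary analysis concerns poison identity.

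The gain from adjustment over the crude test is about 0 to 8 power points for an assumed R² of 0.03 to 0.22. About 1 to 4 points come from factors beyond the coma stratum, under the assumptions in step 5. If the covariates predict death only weakly, the gain is practically nil. In both simulations type I error with adjustment stays near 5%. This is a worthwhile, inexpensive improvement, and the trial would not be unsound without it.

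**What to change.** Before outcomes are examined by arm (the trial is open, so this is the relevant moment), pre-specify a logistic model for in-hospital death with:

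- treatment arm;
- reported time from ingestion to admission, rather than to treatment, because lavage follows stabilisation and its timing may be settled only after randomisation;
- admission coma score;
- amount ingested or underlying disease, only if recorded before randomisation.

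Standardise the fitted risks over the randomised patients to give adjusted RR, ARR and NNT with 95% confidence intervals. Make this the primary estimate, or at least the key supporting analysis, and report the crude table beside it. Keep the planned repeat for poison identity, and amend the limitation in the Discussion to say that measured baseline factors are adjusted for.

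The cost is wording and modest analysis work, with no change to recruitment or care and no new data for the two core covariates. The small downside is that the covariate list and a simple rule for missing baseline values must be fixed in advance.

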## Abbreviations

GLAOP = gastric lavage in acute organophosphorus pesticide poisoning; OP = organophosphorus; RCT = randomised controlled trials; ICU = intensive care unit; ECG = electric cardiac graph; DMEC = data monitoring and ethics committee.
